### Maintenance of randomisation codes and procedures for breaking code

N/A

## TRIAL MANAGEMENT

The Chief Investigator ([name]) has overall responsibility for the trial and shall oversee all trial management. There will be two trial managers ([name], Nottingham and [name], Bristol) who will undertake, jointly, the day-to-day management of the trial. The R&D manager of Nottinghamshire County Teaching PCT ([name]) will have responsibility for financial monitoring and reporting. A study management group (for the NIHR programme grant) comprising all NIHR programme grant co-applicants plus research staff employed to work on all the studies meets three monthly during the duration of the five year programme grant, which will cover the duration of this trial. The trial managers ([name] and [name]) will arrange and manage minuted, telephone conferences every six weeks with researchers in the four centres to ensure consistency of trial process and address queries. Each centre will establish monthly minuted meetings between the PI and the researchers employed on the study.

A Trial Steering Committee (TSC) will be established to oversee the trial. It will meet twice a year with email communication in between the meetings if the independent TSC Chair deems it necessary. The TSC will decide on the appropriateness of establishing a separate data monitoring and ethics committee (DMEC). The TSC will report to the study management group, and to the NIHR via its required interim reports.

## DURATION OF THE TRIAL AND PARTICIPANT INVOLVEMENT

The trial will take place between May 2011 and March 2014. Recruitment of Children’s Centres will take place between May-July 2011 and of families between September-November 2011. Each family that participates in the study will be followed-up 12 months post-recruitment.

### End of the Trial

The trial will be completed when the 12 month follow-up data collection has taken place and the data collection for the implementation process at each Children’s Centre has been completed. Families’ involvement with the trial will finish once the follow-up data collection for the last family has been completed. Children’s Centre managers’ and staff involvement will finish once the implementation process data have been completed and the last interview has been undertaken with Children’s Centre managers and staff.

## SELECTION AND WITHDRAWAL OF PARTICIPANTS

### Recruitment

Children’s Centres

Children’s Centres in the four study coordinating centres who are based in the two or three Primary Care Trusts (PCTs) closest to the study coordinating centres (36 Children’s Centres in 11 PCTs), and who were First-wave Children’s Centres, will be invited to take part in the study by postal invitation followed by a telephone call. The postal invitation will include the study information leaflet, originating from the study coordinating centre research team and the Child Accident Prevention Trust. This will be followed-up by telephone contact with Children’s Centre manager, or a visit to the Children’s Centre, to discuss the study. Those interested in taking part will be sent (or in the case of a visit to a Children’s Centre, will be given) a consent form to complete and return. If more than nine Children’s Centre in each study coordinating centre area agree to take part, nine will be randomly selected.

Families

Families who fit the inclusion criteria will be identified from databases held by Children’s Centres and recruited from the 36 participating Children’s Centres in the four study coordinating centres. There will be several strategies for making the initial approach, depending on which the Children’s Centre staff considers will work best for their population. Combinations of strategies may be used in some centres. Information about the study will be displayed in the relevant areas in each Children’s Centre and each Children’s Centre will use its usual forms of communication to inform families attending the Centre about the trial. This may take the form of posters within the entrance area or specific areas within the Children’s Centre or verbal communication.

1. A study invitation letter, participant information sheet (PIS), baseline questionnaire and a consent form will be posted to parents by Children’s Centre staff. Families will be able to discuss the study with a member of the research team by telephone, or in person, if a researcher is present in the Children’s’ centre at the families next attendance. Families for whom the Children’s Centre would normally use an interpreter will not be sent study invitation letters, instead Children’s Centre staff will be asked to invite these families to the study during an attendance at the Centre when an interpreter is available;
2. A member of the Children’s Centre staff will give parents attending the Centre a study invitation letter, participant information sheet (PIS), baseline questionnaire and a consent form. Parents will have the study explained to them and will be given the opportunity to discuss the study and ask any questions they would like to prior to completing and returning the consent form. This may be in person with the researcher at an arranged time or by telephone;
3. A member of the Children’s Centre staff will approach parents in the Children’s Centre. Parents will have the study explained to them and be given a study invitation letter, participant information sheet (PIS), baseline questionnaire and a consent form. Parents will be given the opportunity to discuss the study with the researcher who will be present within the Children’s Centre and ask any questions they would like to prior to completing and returning the consent form. Where participants are happy to complete the consent form at this point, parents will be invited to complete the questionnaire whilst the researcher and Children’s Centre staff are present. If they do not wish to do this they will be provided with a freepost envelope to return the consent form and completed questionnaire.

If needed, the usual Children’s Centre interpreter and translator services will be available to assist with discussion of the trial, the participant information sheets and consent forms. The consent forms and information sheets will not be available printed in other languages. Participants will only be considered to be recruited to the trial if they complete a consent form and the baseline questionnaire.

### Inclusion criteria

Children’s Centres:

- First-wave Children’s Centres in the four study areas (Nottingham, Newcastle, Bristol and Norwich).

Children’s Centre staff

- Children’s Centre staff who are responsible for the delivery of the IPB in the IPB plus facilitation (I_1_) and the IPB without facilitation (I_2_) arms.

Families

- Any family who has attended the participating Children’s Centre in the previous three months, who have a child under three years old, and lives within the catchment area of that Children’s Centres.

### Exclusion criteria

Children’s Centres:

- Children’s Centres that are not a First-wave Children’s Centre.

Families

- Families who attend a participating Children’s Centre who do not have any children under the age of 3 years
- Any parent who is under-16 years old.

### Expected duration of participant participation

### Children’s Centres will be participating in the trial for 28 months and families will participate for 18 months.

### Removal of participants from the trial

Children’s Centre and family participants may be withdrawn from the trial at their own request. They will be made aware that this will not affect their future care or support from their Children’s Centre. Participants, both Children’s Centres and families, will be made aware (via the information sheet and consent form) that should they withdraw the data collected to date cannot be erased and may still be used in the final analysis. Children’s Centres that withdraw prior to commencement of the intervention will be replaced. Other premature withdrawals will not be replaced.

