## RANDOMISATION AND BLINDING

*Randomisation*

Children’s Centres will be stratified by study coordinating centre (4 strata) and randomly allocated within strata to one of three intervention arms. Randomisation will be conducted by the Newcastle Clinical Trials Unit, using permutable block randomisation, with block size of 9. The allocation code will be will be stored at Newcastle Clinical Trials Unit and only they and each study coordinating centre research team will have access to it. To ensure concealment of allocation each study coordinating centre will only be notified of the allocation of a given Children’s Centre in their area to trial arm once that Centre, and the families within it, have been recruited to the study as described below. This intervention is in addition to information that is already being offered within Children’s Centres. This will minimise post-randomisation recruitment bias. Therefore, parents in both control (‘usual’ care) and intervention Children’s Centres may have received fire-related safety information prior to being allocated to one of the three arms. Parents not recruited to the study will receive whatever information and support that Children’s Centre routinely provides. This may include additional information provided as part of the study. This will be dependent on how Children’s Centres organise the delivery of the IPB. For example, if they offer sessions on preventing house fires they will invite any parent who would normally be invited to these sessions since they will be seen as sessions that a Children’s Centre would provide as part of their ‘usual care’.

The research team in each study coordinating centre will ask Children’s Centres to participate. Once a Children’s Centre has agreed to take part, families from that Children’s Centre will start to be recruited. When the required number of families has been recruited that Centre will be allocated to a treatment arm. To avoid post randomisation recruitment bias, randomisation will only take place after a Children’s Centre and the families within that Children’s Centre have been recruited.

*Blinding*

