**ANALYSES**

# Statistics

### Methods

An analysis plan will be produced by the trial statistician and health economist, who will oversee and/or undertake the statistical and economic analyses.

All analyses will be conducted on an intention-to-treat basis in that families and Children’s Centre managers and staff will be analysed in the group to which they were randomised, regardless of the intervention actually received (eg. if the family moved and used a different Children’s Centre). Analyses will conform to a pre-specified analysis plan and will be undertaken blind to treatment arm allocation.

Characteristics of Children’s Centres and families at baseline will be compared informally between the three treatment arms. The primary outcome measure (having a fire escape plan at 12 months) will be described using frequencies and percentages and compared between treatment arms (I_1_ vs C; I_2_ vs C and I_1_ vs I_2_) using random effects logistic regression to estimate odds ratios and 95% CI. This analysis will have families at level one and Children’s Centres at level two, to allow for clustering of responses within Children's Centres. The primary analysis will adjust for randomisation stratum (study coordinating centre) as a fixed effect and will also adjust for the lead agency of the Children's Centre (Local Authority or NHS led), having a fire escape plan at baseline and deprivation (measured using IMD2007 obtained from families’ postcode). Deprivation has been specified as it is strongly associated with house fire injuries^2,3^ and measures of deprivation have previously been found to be associated with the effectiveness of home injury prevention interventions^18^.

The ICC and 95% CI will be estimated for the primary outcome measure from the regression models. Models will be checked by examining level 2 residuals for normality and constant variance and level 1 and level 2 residuals for outliers.

Sub-group analyses will explore differential effects by deprivation, measured using the IMD2007, by adding interaction terms to the regression model for the primary outcome measure. IMD will be entered as a continuous covariate if there is a linear relationship with outcome.

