### Sample size and justification

11 Children’s Centres per arm will allow an absolute difference in the percentage of families with a fire escape plan of 20% in arm I_1_ or arm I_2_ compared to the control arm to be detected. This assumes a control arm prevalence of 42% (obtained from interviews with parents in Children’s Centres in earlier work in the programme of research), 80% power (2-sided 5% significance), an intraclass correlation coefficient of 0.05 (obtained from interviews with parents in Children’s Centres in earlier work in the programme of research) and that outcomes are assessed on 20 families per Children’s Centre. This gives a total of 33 Children’s Centres. In order that all study coordinating centres recruit the same number of Children’s Centres we will recruit a total of 36 Children’s Centres (9 per study coordinating centre), which will also allow for a potential drop-out of one centre per study arm. In order to achieve outcome data on 20 families per Children’s Centre we will aim to recruit 30 families per Children’s Centre; a total of 1080 families.

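### The rule for replacing centres that withdraw is not limited to withdrawals before randomisation and has no defined cut-off in the control arm

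*Protocol*

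**What the plan says.** Under Removal of participants from the trial, the Protocol states that "Centres that withdraw prior to commencement of the intervention will be replaced" and then that "Other premature withdrawals will not be replaced". It adds that, after a withdrawal, "the data collected to date cannot be erased and may still be used in the final analysis".

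Randomisation and blinding fixes the order of events: "When the required number of families has been recruited that Centre will be allocated to a treatment arm". A coordinating centre learns an allocation only "once that Centre, and the families within it, have been recruited to the study", and the declared purpose is to avoid recruitment bias after randomisation. Blocks are of size nine within four strata. The trials unit and the local research teams have access to the allocation code.

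Methods (under Statistics) requires participants to be "analysed in the group to which they were randomised, regardless of the intervention actually received". Definition of populations analysed limits the full analysis set to families with a follow-up value of the primary outcome. Sample size and justification needs 11 centres per arm and recruits 12, "which will also allow for a potential drop-out of one centre per study arm".

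**The concern.** The cut-off for replacement is the start of the intervention, not randomisation. The Protocol treats these as two events. The recruitment log (Source documents: Case Report Forms) has a field for the date of randomisation and a separate field for the date the intervention started, the latter to be filled only where relevant. Between the two dates a centre can know its arm, decide against it, leave, and be replaced.

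Arm-related withdrawal is plausible because the arms ask for different amounts of work. The facilitated arm involves a training session, a planning meeting and one or more fire safety sessions for participating parents (Facilitation of the IPB and compliance with the intervention). If reluctant centres leave one arm and willing ones take their place, that is selection at cluster level after randomisation. With 12 centres per arm, each centre carries about a twelfth of the arm's result.

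**Working it through.** **Order of events and the control arm.** Recruitment of the centre and its families comes first, then allocation, then the intervention start in the two briefing arms. The Data collection section for Children's Centres times the 12-month centre questionnaire from the intervention start in those two arms and from randomisation in control. Control therefore has no intervention start. Read literally, a control centre is either always before the start or never, and the Protocol does not say which.

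**How a replacement gets its arm.** Nine centres per stratum and a block of nine mean that one block, with 9/3 = 3 centres per arm, is used up in each stratum. A replacement must either take the vacated slot, whose arm the local team may know, or come from a further block. The Protocol describes neither.

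**What happens to the replaced centre.** Its data to date may be kept, but the full analysis set needs a follow-up outcome and the analysis is of complete cases. If its families are not followed up, the centre contributes nothing and the replacement contributes in its place.

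**The planned sample size.** Inputs from Sample size and justification: 42% against 62%, two-sided 5%, power 80%, ICC 0.05, 20 families per centre.
- Design effect = 1 + (20 − 1) × 0.05 = 1.95.
- Two-proportion formula with continuity correction: 107 families per arm; 107 × 1.95 / 20 = 10.43, so 11 centres. This reproduces the Protocol's figure.
- Without the correction: 97 × 1.95 / 20 = 9.46, so 10 centres.

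**Size of a possible bias.** The documents give no withdrawal rate and no figure for how replacements differ, so these are assumptions. Suppose k of 12 centres in one arm are replaced by centres whose prevalence of fire escape plans is d higher. The arm then shifts by k × d / 12.
- Effective families per arm = 12 × 20 / 1.95 = 123.1.
- Unadjusted SE of the difference at 42% = √(2 × 0.42 × 0.58 / 123.1) = 0.063.
- Between-centre SD implied by the ICC = √(0.05 × 0.42 × 0.58) = 0.110, about 11 points.
- Rejection probability under no effect = Φ(−1.96 + shift/SE) + Φ(−1.96 − shift/SE).

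| Assumed replacement | Shift (points) | Actual error at nominal 5% |
|---|---|---|
| 1 centre, 1 SD higher | 0.9 | 5.2% |
| 1 centre, 15 points higher | 1.25 | 5.5% |
| 2 centres, 1 SD higher | 1.8 | 6.0% |
| 2 centres, 15 points higher | 2.5 | 6.8% |
| 3 centres, 20 points higher | 5.0 | 12.5% |

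**Power if nobody is replaced after randomisation.** Effective n per arm = centres × 20 / 1.95.

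| Centres per arm | No continuity correction | With correction |
|---|---|---|
| 12 v 12 | 88.6% | 85.9% |
| 12 v 11 | 87.2% | 84.2% |
| 11 v 11 | 85.7% | 82.4% |
| 11 v 10 | 84.0% | 80.4% |
| 10 v 10 | 82.3% | 78.3% |

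**The case against.** The strongest reply is that the Protocol never says a replaced centre leaves the analysis. It keeps the intention-to-treat statement, allows data to date to be used, has families consent individually, and promises efforts to stay in contact with them. A reader might infer that the rule breaks intention-to-treat outright; the text does not go that far. The handling of a replaced centre may also be set out in a statistical analysis plan that is not shown. What remains is that the rule and the analysis set together make a swap the likely practical result.

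A reader might also infer that replacements are recruited with their arm already known. The documents do not establish this. A coordinating centre "will only be notified of the allocation of a given" centre's allocation after recruitment, no exception is made for replacements, and the trials unit could randomise a replacement afresh. The supportable statement is that the route is not specified, and that one of the two possible routes would undo concealment.

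On size, the primary model adjusts for having a plan at baseline, deprivation, lead agency and stratum. Every recruited family must complete a baseline questionnaire, so replacement families would have the baseline value. It would therefore be wrong to say that no covariate helps: part of a baseline difference would be removed. Differences in willingness to implement would not be. The 12.5% figure needs three of 12 centres replaced, each by one 20 points higher (20/11.0 = 1.8 SD), all in one direction and with no adjustment. That is an extreme case.

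Finally, the same sentence covers withdrawals before randomisation, and replacement there is unobjectionable.

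**Conclusion.** The point holds in limited form. The rule permits replacement of clusters after randomisation, has no defined meaning in the control arm, and leaves open the allocation of the replacement and the treatment of the replaced centre. This sits badly with the intention-to-treat statement and with the aim of avoiding recruitment bias after randomisation. It is an ambiguity with a route to bias, not a proven breach of either.

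The likely effect is modest: an error of roughly 5.2–6.8% against a nominal 5% for one or two swaps in one arm. This rests on replacements being 11 to 15 points higher, all in the same direction, and on an unadjusted SE. The rule should be fixed because it is a conduct rule whose effect later analysis can only partly undo, and because the planned power does not depend on it.

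**What to change.** Amend Removal of participants from the trial to say:
- only centres that withdraw before randomisation are replaced;
- centres that withdraw after randomisation, in any arm, are not replaced and remain in their allocated arm for analysis;
- their individually consented families are still sent the follow-up questionnaire unless they themselves withdraw.

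Using randomisation as the cut-off gives the rule the same meaning in all three arms and removes the need to allocate a replacement once the block is used up.

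The cost is a short amendment and the chance that an arm ends with 11 centres. The 11 + 1 allowance already covers that: power is 82.4–85.7% at 11 v 11. It falls below 80% only at 10 v 10, and only with the continuity correction (78.3%).

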### Informed consent

The process for obtaining participant informed will be in accordance with the REC guidance, Good Clinical Practice (GCP) and any other regulatory requirements that might be introduced. Parents recruited face-to-face in Children’s Centres will have the trial explained to them by a member of the research team or Children’s Centre staff and will be given a PIS. Parents will be able to ask the researcher any questions concerning participation in the study or be given the research team contact details. Participants will be able to sign the informed consent form (ICF) at this time, or take it home and sign at a later date and return to the study team by post. Families recruited postally will be given the telephone number of the research team whom they can contact to discuss the study and have an opportunity to ask questions about the study. They can complete, sign and date the ICF at a time of their choosing and return it to the researchers in a freepost envelope. All ICFs will be signed and dated by the parent and the researcher. The original ICF will be kept by the study coordinating centre in the trial master file and a copy will be sent to/kept by each participant. ICFs returned by post will be signed and dated by the researcher prior to the copy being sent to the parent. ICFs will be completed prior to the delivery of any intervention. On receipt of an ICF the relevant Children’s Centre will be informed of that family’s participation.

Children’s Centre managers will be sent a PIS about the trial, with information that relates to both the Centre’s anticipated involvement and the family participants. They will have the opportunity to discuss the study by telephone or face-face with a member of the research team and be given the opportunity to ask any questions about the trial. They will be asked to sign an ICF, which will then be signed by the researcher. The original ICF will be kept by the study coordinating centre in the trial master file and a copy will be sent to/kept by each participating Children’s Centre. ICFs returned by post will be signed by the researcher prior to the copy being sent to the Children’s Centre. ICFs will be completed prior to randomisation. Each Children’s Centre manager and/or staff who are interviewed to explore barriers and facilitators to implementing the IPB will complete, sign and date a separate ICF prior to the interview. Two copies will be completed and signed and dated by the researcher, one copy will be kept by the interviewee and the other will be kept by the study coordinating centre in the trial master file.

Should there be any subsequent amendment to the protocol, which might affect a participant’s participation in the trial, the investigator shall follow all applicable regulatory requirements pertaining to approval of the amended Consent Form by the REC and use of the amended form (including for on-going participants). Continuing consent will be obtained using an amended Consent Form which will be signed by the participant.

Data collection

